#### Study treatment

Anxiety treatment was informed by a flexible treatment manual used by our research team in previous exposure training studies (54, 55), as well as treatment strategies employed as usual practice. The study explicitly did not require use of a specific treatment protocol, but instead encouraged “flexibility within fidelity” to the provided manual by applying a workshop knowledge about exposure principles and their intended function on patients’ presenting concerns (60). Rather, therapists were oriented to a flexible manual that outlined the basic ‘steps’ needed to support exposure, but left room for therapists to independently apply the exposure principles detailed during the workshop. Length of treatment and timing of treatment sessions (e.g., daily, every other day) was variable depending on usual care at the organization (i.e., some insurances require more face-to-face hours than others for reimbursement of home-based service packages). End of treatment as part of study participation was triggered by one of the following: (1) formal treatment termination with therapist, (2) patient no longer interested in participating in the research study, or (3) patient and therapist agree that anxiety is no longer the primary focus of treatment and switch to a new target for which exposure is not the primary treatment.

## Anticipated results

The primary goals of this study are to first establish and then confirm engagement of the negative beliefs target with the novel E2E training approach, and to also demonstrate a relationship between change in the beliefs target and therapists’ in-session delivery behaviors. Target engagement was established during the Phase 1 trial. The Phase 2 training trial will confirm target engagement by demonstrating significantly greater change in belief scores following workshop training for therapists assigned to E2E relative to the didactic group (Hypothesis 1). To test this effect, group status (E2E vs. didactic) will be entered as a predictor of post-workshop total TBES score while including a random intercept for TBES baseline score. It is anticipated that as TBES-measured belief levels approach zero, the distribution will become positively skewed. This is problematic given the goal to target and reduce belief levels as close to zero as possible. To account for the positive skew of TBES scores approaching zero, binomial-based modeling will be used to conduct a logistic regression to assess for a difference in belief reduction between those in the didactic and E2E groups following the workshop training. Figure 3 illustrates the measurement time points and pathways for testing planned hypotheses.

It is also expected that the E2E intervention will produce a specific change in negative beliefs (measured pre-and post-workshop) about exposure but not differentially affect broader beliefs about EBPs (EBPAS) in general (Hypothesis 2). Target specificity will be demonstrated by significantly greater levels of negative belief change but comparable levels of EBP belief change in the E2E group relative to didactic. The pilot nature of this study does not allow sufficient statistical power to conduct a non-inferiority test of group differences on EBPAS change, so comparison of descriptive statistics will provide initial evidence of specificity to be fully tested in a larger trial (61, 62).

The relationship between target change (i.e., reduction in negative beliefs) and outcomes of interest will be evaluated using the EPCS micro-analytic coding system for categorizing in-session exposure delivery behavior (Hypothesis 3). Therapist delivery behaviors during the consultation phase of training will be categorized into “optimal” (i.e., delivery behaviors intended to engage and intensify patient anxiety) and “suboptimal” (i.e., delivery behaviors intended to artificially reduce patient anxiety) categories in accordance with previously established procedures (54). Rates of optimal and suboptimal delivery behaviors will be calculated for each therapist with recorded session data, and in-session behavior will be examined as a function of post-training TBES scores using GLM (Gaussian distribution); these will be conducted as two separate tests examining optimal and suboptimal behaviors. Finally, the relationship between negative beliefs and rates of exposure utilization, calculated as a percentage of sessions with and without exposure delivery, will be assessed using correlational analyses consistent with past training trials incorporating the EPCS coding system [(54, 55); Hypothesis 4].

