Evaluation of the exposure to exposure (E2E) training intervention took place in two phases. The first phase was a case-series analysis (*N* = 6 therapists) intended to fine-tune training procedures and establish the necessary dose of experiential training for therapists’ negative belief levels to reach an *a-priori* benchmark. The second phase was a randomized trial (*N* = 36 therapists) testing whether the targeted E2E training approach, relative to didactics alone, was a more potent intervention for reducing negative beliefs. Specifically, it was hypothesized that therapists in the E2E training condition would evidence significantly lower negative beliefs about exposure relative to the didactic condition at post-workshop. As an added layer of rigor, levels of general beliefs about EBP were measured along with negative beliefs at pre-, mid-, and post-workshop to demonstrate the specificity of the E2E condition’s effect on the planned target (i.e., negative beliefs) while exhibiting comparable levels of EBP belief change relative to the didactic condition. It was also hypothesized that negative belief change during the workshop training would be associated with therapist delivery behavior when implementing exposure with anxious patients in the consultation phase of the study, such that greater reduction in negative beliefs would be associated with: (1) a higher rate of optimal delivery behaviors, (2) a lower rate of suboptimal delivery behaviors as measured by both self-report and observational coding data, and (3) a higher rate of exposure utilization across sessions. A detailed accounting of study methods, practical adjustments, and other implementation considerations are presented below.

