### Measures

#### Therapist workshop measures

Therapist negative Beliefs about Exposure Scale [TBES; (23)]. The TBES assesses the extent to which therapists endorse 21 negative beliefs about exposure therapy. Participants use a 5-point scale (0 = “disagree strongly” to 4 = “agree strongly”) to indicate the extent to which they agree with such items as “most clients have difficulty tolerating the distress exposure therapy evokes.” The TBES is the primary outcome measure for assessing target engagement. Evidence Based Practice Attitudes Scale [EBPAS; (52)]. This is a brief (15-item) measure that assesses four general attitudes toward adoption of EBPs, including such items as “research based treatments are not clinically useful.” This measure will be used to demonstrate the specificity of target engagement with the E2E approach. Specificity is exhibited by the extent to which the training groups differ on belief change while remaining equivalent in attitudes about EBP in general. Exposure Knowledge (36). We have condensed the original 49 multi-choice item measure by selecting 12 multiple-choice items that best fit the didactic content of our training, for instance, “Why is it important to block avoidance during exposure tasks?” Exposure Self-Efficacy (36). This is a 27-item measure of therapists’ confidence in delivering exposure therapy. All items began with “I feel confident in my ability to,” and an example item is “Conduct imaginal exposure.” Items are rated on a 5-point Likert scale ranging from 1 (not confident) to 5 (very confident). This measure has demonstrated high internal consistency and predictive validity in determining the frequency of self-reported clinical use of exposure therapy. Beliefs about Exposure Scale-Training (BES-T). This is a beliefs process measure designed for this study to measure belief change during training activities. The scale consists of six items that assess therapists’ reservations about the safety and tolerability of exposure therapy. The first five items are rated on a 0 (“Completely Disagree”) to 100 (“Completely Agree”) scale and assess perceptions of safety and tolerability of exposure for their patients as well as themselves. The sixth item stated, “I feel very confident in my ability to deliver exposure therapy and I am committed to using it with my anxious clients,” and the response options were either “Not Yet” or “No more practice – I am ready.” Therapists continued with experiential tasks until they endorsed the “I am ready” item. This item is a go/no-go item intended to solicit self-perceptions of whether therapists felt ready and able to use exposure therapy patients with anxiety. Training Acceptability Rating Scale [TARS; (53)]. The TARS is a measure of therapists’ satisfaction with trainings that has good psychometric properties. Participants rate training acceptability and perceived utility on Likert scales (total scores = 6–63), in addition to qualitative feedback.

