#### Phase 2: Randomized training trial (ongoing)

Therapists were randomly assigned to either a didactic-only or a didactic plus E2E training workshop which was 12 h in total. All therapists completed the same 8-h “Core Workshop,” which was followed by a condition-specific 4-h training (Didactic or E2E). Following the workshop training, therapists began using exposure therapy with patients presenting with anxiety disorders and received ongoing weekly consultation. Each therapist was encouraged to refer 1–2 patients to the study to receive ongoing consultation regarding the use of exposure therapy for patients who elected to participate in the study. In line with the gold-standard structure for therapist training, therapists with enrolled patients attended weekly, hour-long consultation conducted in a group format *via* video teleconferencing.

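### The Hypothesis 1 model enters baseline TBES only as a random intercept, which adjusts for baseline incidentally and inefficiently; it should be a fixed covariate in the planned binomial model

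*Protocol article*

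**What the plan says.** Under Therapist workshop measures, the article states: "The TBES is the primary outcome measure for assessing target engagement". The scale has 21 items scored 0 to 4, so the total runs from 0 to 84.

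Under Anticipated results, Hypothesis 1 is greater change in beliefs in the E2E arm than in the didactic arm. The model is given in one sentence: "group status (E2E vs. didactic) will be entered as a predictor of post-workshop total TBES score", "while including a random intercept for TBES baseline score". To deal with skew as scores approach zero, the article adds that "binomial-based modeling will be used to conduct a logistic regression to assess for a difference in belief reduction".

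Baseline TBES enters this model nowhere else. The text gives no fixed covariate, no change score as outcome and no group-by-time term.

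**The concern.** A random intercept belongs to a grouping factor whose levels contribute several observations, such as a therapist measured repeatedly or a clinic with many therapists. Baseline TBES is a near-continuous score, and the stated outcome supplies one value per therapist. If software is told to use baseline TBES as the grouping factor, each distinct score becomes a level, and the level effects are treated as exchangeable draws. The model then has no way to know that a therapist starting at 60 should be expected to finish higher than one starting at 20.

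This matters because the baseline score is the obvious source of extra precision in a trial of 36, and Hypothesis 1 is about change. If the term does not estimate the baseline-to-post relation, most of that precision is given up, and a chance difference between arms at baseline is only partly taken out of the group effect.

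**Working it through.** **Inputs from the article.** 36 randomized therapists; TBES range 21 × 4 = 84; one post-workshop total per therapist; binomial family. The article states no SD, correlation, effect size or power for this test, so there is no figure of its own to reproduce.

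**Assumed inputs.** 18 per arm (the ratio is not stated); baseline-post correlation ρ = 0.3, 0.5 and 0.7; baseline SD 8, 12 and 16 in the Gaussian runs and 12 in the binomial runs; no true group effect. The binomial runs treat the total as points out of 84.

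**Step 1: what the clusters look like.** With rounded baseline scores, 36 therapists give on average about 21 to 27 distinct values. At SD 12 there are about 25, or 36 / 25 = 1.4 therapists per level. The random intercept is therefore nearly confounded with residual error.

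**Step 2: how large chance imbalance is.** The SD of the difference in baseline means is √(2/18) = 0.33 baseline SDs, or 0.33 × 12 = 4 points if the SD is 12.

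**Step 3: Gaussian version, baseline SD 12, 600 runs per cell.**

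| | ρ = 0.3 | ρ = 0.5 | ρ = 0.7 |
|---|---|---|---|
| SD of group effect, random intercept | 3.93 | 4.09 | 3.79 |
| SD, unadjusted | 3.90 | 4.03 | 3.83 |
| SD, fixed baseline covariate | 3.78 | 3.53 | 2.76 |
| Shift per point of imbalance, random intercept | 0.32 | 0.46 | 0.52 |
| Shift, unadjusted | 0.33 | 0.50 | 0.67 |
| Shift, fixed covariate | 0.03 | 0.03 | −0.03 |

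The random intercept performs almost like no adjustment. Over all nine cells the retained share of the imbalance effect runs from 0.49/0.72 = 68% to 0.32/0.33 = 97%. At ρ = 0.5, a one-SD imbalance of 4 points moves the estimate by 4 × 0.46 = 1.8 points, against 4 × 0.03 = 0.1 with the covariate.

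**Step 4: variance that a covariate can remove.** In the Gaussian approximation the variance is multiplied by 1 − ρ² = 0.91, 0.75 and 0.51, a reduction of 9%, 25% and 49%. The simulated ratios to the random-intercept model agree: (3.78/3.93)² = 0.93, (3.53/4.09)² = 0.74, (2.76/3.79)² = 0.53.

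**Step 5: binomial version, the planned family, 250 runs per cell.** The comparator has a fixed baseline covariate plus a therapist-level random effect.

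| | ρ = 0.3 | ρ = 0.5 | ρ = 0.7 |
|---|---|---|---|
| SD of log-odds effect, random intercept | 0.284 | 0.260 | 0.214 |
| SD, covariate plus therapist effect | 0.225 | 0.179 | 0.161 |
| Shift per baseline SD of imbalance, random intercept | 0.051 | 0.147 | 0.111 |
| Shift, covariate plus therapist effect | −0.011 | 0.049 | −0.015 |

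The data were generated with a logit slope of 0.6ρ = 0.18, 0.30 and 0.42 per baseline SD, which is roughly what an unadjusted analysis would carry. The random intercept therefore keeps about 0.051/0.18 = 28%, 0.147/0.30 = 49% and 0.111/0.42 = 26%. These shares are imprecise: the Monte Carlo error of the slopes is about 0.284/(0.333 × √250) = 0.05 at ρ = 0.3 and 0.04 at ρ = 0.7.

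Tied scores thus remove more imbalance here than in the Gaussian model, but at a price. With logit variance 0.6² = 0.36, and binomial variance about 1/(84 × 0.29 × 0.71) = 0.06 at the generating intercept of −0.9, an unadjusted log-odds contrast has an SD of about √((0.36 + 0.06) × 2/18) = 0.22. The random-intercept SDs of 0.284 and 0.260 at ρ = 0.3 and 0.5 are larger than that; at ρ = 0.7 the 0.214 is about equal to it.

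**The case against.** **The phrase may be loose wording.** The authors may have meant an ordinary baseline covariate, or a therapist random intercept in a repeated-measures model. The article condenses a fuller plan and refers to a figure for its testing pathways. This stands as a limit: the harm arises only if the sentence is followed as written. It does not remove the point. Those are two different models, the sentence describes neither, and its stated outcome is the post-workshop score alone. All 36 Phase 2 therapists have completed the workshop, so the choice should be settled before it can be informed by the results.

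**The size is uncertain.** Every SD and correlation above is assumed, and at ρ = 0.3 the possible gain is small. This stands. The 68% to 97% retention comes from a Gaussian model that the article does not plan. The binomial comparison changes two things at once, the covariate and the handling of overdispersion, so its whole gain cannot be credited to the covariate.

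**It is a pilot, and randomization protects the comparison.** The Discussion disclaims a fully powered test, and Current study also words the hypothesis as lower beliefs at post-workshop, which is a post-score contrast. Under randomization both wordings target the same expected difference. This stands against any claim of bias, but not against wasting a measurement already taken.

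**Readings that go too far.** A reader might infer that Hypothesis 1 has no baseline adjustment at all, or is biased. Tied scores give some adjustment, and randomization keeps the estimate unbiased on average. A reader might also infer that the analysis must become a Gaussian ANCOVA, or must add the end-of-core-didactics TBES. The first would contradict the binomial modelling that the article chooses for skew. The second score was probably taken after randomization, so using it is a debatable trade-off and its absence is not an error.

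**Conclusion.** The point holds for the model as written. Baseline TBES as a random intercept is a misspecified term: it estimates no baseline-to-post slope and adjusts only where scores happen to tie. The consequence is lost precision and incomplete removal of chance imbalance, not average bias.

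The removable variance is about 9% to 49% for ρ between 0.3 and 0.7, in a Gaussian approximation with 18 per arm. In the planned binomial family the direction is the same under the assumed inputs. Most of the chance imbalance survives in the Gaussian version, and roughly a quarter to a half in the binomial version, which has the larger precision loss at the lower correlations.

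A reader might infer a definite loss of power for Hypothesis 1. The documents do not support a figure, since they give no SD, correlation or target effect and claim no power.

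**What to change.** Keep the binomial model and change how baseline enters. Suggested wording: *Post-workshop TBES total (out of 84) will be analysed in a binomial model with group and baseline TBES as fixed effects, allowing for overdispersion by a therapist-level random effect or quasi-binomial errors; the adjusted group effect will be reported with its 95% confidence interval.*

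An acceptable alternative is to model baseline and post-workshop TBES jointly, with a therapist random intercept and a group-by-time term that carries the Hypothesis 1 test. One of the two should be named before the Phase 2 TBES data are compared between arms.

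The fixed covariate costs one model degree of freedom, and neither option needs new data. Neither a Gaussian ANCOVA nor the mid-workshop TBES as a covariate is needed.

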#### Turnover

Initiation of the phase two randomized training trial coincided with the onset of COVID and required a retooling of all planned in-person components to occur remotely (i.e., consenting, measure administration, recruitment, and all training and consultation activities). After piloting and obtaining IRB approval for remote study procedures, the first training was well-attended because therapists were struggling to generate clinical revenue while clinics transitioned to remote care options. Thus, therapists eagerly signed up for the training but had few patients to refer for the consultation component, which contributed to patient recruitment difficulties early in phase two. Relatedly, the “great resignation” (67) occurred during the trial and 57% of trained therapists left their organization during phase two, which again affected patient recruitment rates. Patients were recruited to the study to allow for in-session measures of therapist delivery behavior following training, so patient participants needed to be assigned to a study therapist in order to be eligible for participation. As therapist turnover escalated, the pool of eligible participants shrunk and necessitated an over-recruitment of therapists (36 trained therapists rather than 26 originally proposed) in order for patient recruitment to continue.

Although resources exist to help guide a thorough needs assessment prior to initiating implementation activities in a partnering organization [e.g., (68)], there is much less guidance for implementing therapist training interventions in collaboration with CMHAs. Based on implementation experiences in the current study, it is recommended that early assessment and planning include a thorough understanding of how agency personnel are related hierarchically and with regard to clinical tasks relevant to the study intervention. If there are changes to partnering agencies, sites, or key personnel, as is common when conducting community-based training interventions, it is worth reassessing the organization hierarchy and job duties of all relevant staff to prevent some of the implementation challenges encountered in this study.

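### Hypothesis 1 puts a binomial/logistic model on the 0–84 TBES total with an ill-defined random intercept and no stated overdispersion term; on the literal and repeated-measures readings, type I error could be about 10–50%

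*Protocol article*

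**What the plan says.** Under Therapist workshop measures, "The TBES assesses the extent to which therapists endorse 21 negative beliefs about exposure therapy", each item scored on a 5-point scale from 0 to 4. The same section states that "The TBES is the primary outcome measure for assessing target engagement".

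Under Anticipated results, group status "will be entered as a predictor of post-workshop total TBES score". Baseline comes into the model through a separate clause, "while including a random intercept for TBES baseline score". The choice of distribution is given a few sentences later: "binomial-based modeling will be used to conduct a logistic regression to assess for a difference in belief reduction". The motive offered for that choice is "To account for the positive skew of TBES scores approaching zero". The Phase 2 trial is meant to confirm target engagement by showing a significantly greater change in the E2E arm.

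The article does not say how many trials the binomial has, whether the score is kept as a total or cut into a yes/no outcome, or which unit the random intercept is grouped on. It mentions no dispersion parameter and no robust variance. The only reason given for the binomial family is skew; variance is not discussed.

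**The concern.** A binomial model of a 0–84 total treats each therapist's score as 84 independent yes/no trials. The score is really a sum of 21 ordinal items answered by one person, and a therapist who fears exposure on one item tends to fear it on others. That correlation makes totals vary between therapists by more than the binomial allows. If the model has nowhere to put the extra variance, the standard error of the group effect is too small.

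The random intercept does not clearly supply that place. Baseline TBES is a measured covariate, not a grouping factor. Taken literally, the phrase gives therapists with the same baseline score a shared intercept and treats any remaining difference between them as pure binomial noise. It also drops the ordinary regression of post score on baseline.

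At stake is the test on which the claim of target engagement rests. With an anti-conservative test, a training that adds nothing beyond didactics could appear to have engaged its target and be carried into the larger trial.

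**Working it through.** The article states no SD, alpha, power or error rate for this test, so there is no figure of its own to reproduce.

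**Inputs from the article.** 21 items scored 0–4, so the maximum total is 21 × 4 = 84. Phase 2 trained 36 therapists ("36 trained therapists rather than 26 originally proposed").

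**Assumptions.** 1:1 allocation (18 per arm), two-sided 5% test, a post-workshop mean near 20, and a range of SDs and baseline–post correlations r.

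**Analytic check.** The binomial variance is 84·p·(1−p) with p = mean/84. At mean 20 this is 20 × 64/84 = 15.24, an SD of 3.9. With true SD s, the dispersion left after baseline adjustment is φ = s²(1−r²)/15.24. The actual two-sided error of a nominal 5% test is 2·[1 − Φ(1.96/√φ)].

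| Assumed SD | φ, r = 0 | Error, r = 0 | φ, r = 0.7 | Error, r = 0.7 |
|---|---|---|---|---|
| 5 | 1.64 | 13% | 0.84 | 3% |
| 6 | 2.36 | 20% | 1.20 | 7% |
| 8 | 4.20 | 34% | 2.14 | 18% |
| 10 | 6.56 | 44% | 3.35 | 28% |
| 12 | 9.45 | 52% | 4.82 | 37% |

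**Which SDs are plausible?** Suppose each item had the binomial-equivalent variance. Then φ = 1/(1 − α·20/21), where α is the scale's internal consistency. For α of 0.70, 0.80 and 0.90, φ is 3.0, 4.2 and 7.0, and the error at r = 0 is 26%, 34% and 46%. An SD of 5 would correspond to α of about (1 − 1/1.64) × 21/20 = 0.41, which sits uneasily with the Introduction's description of the scale's psychometric properties as acceptable. Floor effects after the workshop could lower item variance or α, so this is a guide and not an estimate.

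**Simulation under no group effect.** 36 therapists; 21 items scored 0–4, correlated through a person factor; post-workshop mean about 21; SD 6.5–12.3; latent baseline–post correlation 0.3 or 0.7; 400–1,000 runs per setting.

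| Reading of the plan | Type I error |
|---|---|
| Binomial out of 84, baseline as fixed covariate, no random effect (reference) | 17–48% |
| Binomial out of 84, intercept grouped by baseline value (literal) | 15–50% |
| Binomial out of 84, baseline and post as repeated measures, therapist intercept | 9–41% |
| Binomial out of 84, one intercept per therapist, post score only | 5–8% |
| Dichotomised TBES, logistic regression | 4–6% |

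On the literal reading, the 36 simulated therapists had only about 20–26 distinct baseline values, so many shared an intercept. With uncorrelated items (SD 3.8, φ = 0.96) the reference model gave 3%. Item correlation is therefore what drives the inflation.

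**The case against.** The strongest reply is that the sentence is ambiguous and some readings are sound. The article never says the total is treated as 84 trials. The term binomial-based could cover quasi-binomial or beta-binomial models, and a condensed article may leave dispersion to the full plan. One intercept per therapist on the single post score would absorb the extra variance. A dichotomised outcome cannot be overdispersed in this way. The SD and mean are assumed, and unadjusted calculations overstate the problem when baseline predicts the post score well. Finally, the Discussion says the pilot sample is not meant as a fully powered test of group differences.

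Much of this stands. A reader might infer that the primary test certainly has a false-positive rate far above 5%, or that the investigators have decided against any dispersion term. The article supports neither: the denominator and grouping unit are unstated, the SD is not given, and silence on dispersion in a condensed report is not a decision against it.

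It does not remove the point. The article fixes the model family, names the total as the response and attaches the random intercept to the baseline score, not to the therapist. The most literal reading is one of those that fail. Dichotomising would contradict the total-score response. Measurement considerations mentions a TBES criterion, but Hypothesis 1 is not written in terms of it. The pilot caveat concerns power and does not excuse an inflated false-positive rate.

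**Conclusion.** The concern holds conditionally. If the TBES total is modelled as successes out of 84, with the intercept grouped by baseline value or with baseline and post scores as repeated measures, the standard error is too small and type I error could be about 10–50%. That range rests on assumed post-workshop SDs of about 6–12, 18 therapists per arm and a mean near 20. At the low end of the SD range with r = 0.7 the analytic figure is about 7%, and at an SD of 5 with r = 0.7 there is no inflation.

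Among the readings examined that use the stated model without an added dispersion term, error is near nominal only with one intercept per therapist on the post score or with a dichotomised score. The first is not what the text says. The second departs from the stated response and discards most of the scale. Anticipated skew near zero requires neither the uncorrected binomial variance nor a cut-point.

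**What to change.** State that the response is the post-workshop TBES total and enter baseline TBES as a fixed covariate in place of the random intercept. Then choose one of two analyses:

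- a quasi-binomial or beta-binomial model for the 0–84 score, with the dispersion estimated from the data; or
- ANCOVA on the total, with a permutation or robust p-value to deal with skew.

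Either is acceptable. In the simulated data above, quasi-binomial with a fixed baseline gave 4.0–6.1% type I error, and ANCOVA with its ordinary p-value gave 4.2–6.3%. The beta-binomial model and the permutation and robust p-values were not simulated. Do not dichotomise for the primary test. If a yes/no summary is wanted, report the proportion in each arm below the a-priori TBES criterion used in Phase 1 as a descriptive supplement.

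Only the analysis wording changes; no new data are needed. The price is a p-value less favourable than the uncorrected binomial model would produce.

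### Hypothesis 2 rests target specificity on a significant TBES difference beside EBPAS descriptives judged comparable, which does not show that the two effects differ

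*Protocol article*

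**What the plan says.** The Current study section presents the EBPAS comparison as extra rigour: E2E should move negative beliefs while "exhibiting comparable levels of EBP belief change relative to the didactic condition". Therapist workshop measures gives the definition: "Specificity is exhibited by the extent to which the training groups differ on belief change while remaining equivalent in attitudes about EBP in general".

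Anticipated results turns this into a rule for Hypothesis 2: "Target specificity will be demonstrated by significantly greater levels of negative belief change but comparable levels of EBP belief change". The same paragraph says that the pilot "does not allow sufficient statistical power to conduct a non-inferiority test of group differences on EBPAS change", and so "comparison of descriptive statistics will provide initial evidence of specificity to be fully tested in a larger trial".

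The Turnover section gives the sample size: "36 trained therapists rather than 26 originally proposed". The article gives no between-group effect size, allocation ratio, significance level or threshold for comparable change.

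**The concern.** Specificity is a statement about the difference between two effects: E2E moves exposure beliefs more than it moves general attitudes to evidence-based practice. The rule tests one effect for significance, inspects the other, and draws the conclusion from the pair. A significant effect on one scale and an effect on another that merely looks similar between groups can arise when the two true effects are close, or even equal.

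There is also a mismatch of direction. Equivalent and comparable change are two-sided ideas: a gain in EBPAS under E2E would undermine specificity as much as a loss. A non-inferiority test guards against one direction only. This trial will not run that test, but the article points to a larger trial for the full test, so the wrong label could carry forward.

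At stake is the interpretation of the mechanism. The article offers the study as a template for mechanism testing, and the specificity check is part of what supports attributing change to the belief target.

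**Working it through.** The article gives no power or precision figure for this comparison, so there is nothing to reproduce. The check asks what the stated rule can distinguish.

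**Inputs**
- From the article: 36 therapists; a significant TBES difference is required; EBPAS is judged from descriptive statistics.
- Assumed: 1:1 allocation (18 per arm), two-sided 5% level, two-sample t-tests on standardised change scores aligned so that improvement is positive, true effects of 0, 0.5 or 0.8 SD, and a correlation of 0.4 between the scales.
- Also assumed, because no threshold is given: four readings of comparable, namely observed |d| below 0.2, 0.3 or 0.5, or a non-significant difference.

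**Precision of the EBPAS difference**
- Unadjusted 95% half-width = t(0.975, 34) × √(2/18) = 2.032 × 0.3333 = 0.68 SD.
- Baseline adjustment multiplies this by √(1 − r²): 0.677 × 0.866 = 0.59 SD at r = 0.5, and 0.677 × 0.714 = 0.48 SD at r = 0.7.
- So identical observed EBPAS means would still leave an unadjusted interval of about −0.68 to +0.68 SD.

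**How often the specificity pattern appears** (simulation at 18 per arm, correlation 0.4; TBES significant and EBPAS read as comparable)

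| True effects (TBES, EBPAS) | \|d\| < 0.2 | \|d\| < 0.3 | \|d\| < 0.5 | non-significant |
|---|---|---|---|---|
| 0.8, 0.8 | 1% | 2% | 8% | 17–18% |
| 0.8, 0.5 | 7% | 12% | 26% | 40% |

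In the first row there is no specificity at all. In the second the effects do differ, by 0.3 SD, but EBPAS change is not comparable between the groups.

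**The direct contrast** (TBES effect minus EBPAS effect, both in SD units)
- SD of the difference score = √(2 × (1 − 0.4)) = 1.095.
- 95% half-width = 0.677 × 1.095 = 0.74 SD.
- With equal true effects, it wrongly favours TBES in about 2.5% of trials, as expected of a two-sided 5% test.
- With true effects of 0.8 and 0: standardised difference 0.8 / 1.095 = 0.730; noncentrality 0.730 / 0.3333 = 2.19; power about 0.57. Across correlations from 0 to 0.5, the simulated power runs from 0.38 to 0.65.

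The simulation uses t-tests rather than the planned binomial-based TBES model and ignores clustering by workshop group. It shows order of magnitude only.

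**The case against.** **The article already limits the claim.** It says that power is lacking, labels the result initial evidence, defers the full test to a larger trial, and says in the Discussion that the sample is not meant as a fully powered test of group differences. This stands. A reader might infer that the study would declare specificity established by default, and the documents do not support that reading. What remains is that the same paragraph says specificity will be demonstrated, and that low power is a reason to show the uncertainty, not to leave it out.

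**No EBPAS significance test is planned.** A reader might argue from power alone: an EBPAS effect of 0.8 SD would be non-significant in about 35% of trials and one of 0.5 SD in about 69%. Those rates assume a test that the plan does not run, and they ignore the requirement that TBES also be significant. Under a strict descriptive reading, an equal EBPAS effect would seldom pass (about 1%).

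**Knowledge and self-efficacy.** Table 1 lists both as candidate targets, and a reader might infer that omitting them from the specificity check is an error. Hypothesis 2 claims specificity only against general attitudes to evidence-based practice, and Table 1 gives that role to EBPAS alone. Adding the others is a preference.

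**Analysis detail may sit in a fuller plan.** A margin or model specification may well be there, and its absence here is no fault. The rule itself and the name of the test are stated in the article and can be judged. An equivalence margin would in any case help little: the unadjusted 90% half-width is 1.691 × 0.3333 = 0.56 SD, so equivalence could not be shown at 0.5 SD or tighter on that analysis.

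**A common scale is needed.** The article expects TBES to skew towards zero and plans binomial-based modelling, so a TBES-minus-EBPAS contrast requires both effects in standardised units. That is a fair constraint, and the fix allows for it.

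**Conclusion.** The point holds as one about inference and wording on an openly preliminary hypothesis. A significant TBES difference beside an EBPAS difference judged by eye does not show that the effects differ, and an EBPAS effect of up to about 0.68 SD (unadjusted) would remain compatible with identical observed means. Depending on how comparable is read, the pattern would appear in about 1% to 18% of trials with equal 0.8 SD effects, and in about 7% to 40% with effects of 0.8 and 0.5 SD. The width of those ranges is itself the cost of leaving the term open. Separately, non-inferiority does not match a two-sided claim; this changes no result of the present trial.

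The figures rest on assumed 18 per arm, a two-sided 5% level, correlation 0.4 and the stated effect sizes, none of which the article supplies. The conclusion that the rule does not compare the two effects needs none of them.

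**What to change.** 1. Report the baseline-adjusted EBPAS group difference with its 95% CI alongside the descriptive statistics.
2. Add the contrast of the TBES group effect minus the EBPAS group effect, on a common standardised scale with both scored in the same direction, and its 95% CI. Base any specificity statement on it, and report specificity as not established if the interval includes zero.
3. Replace non-inferiority with equivalence, here and in the design of the larger trial.
4. Change the statement that specificity will be demonstrated to one that it will be explored, in line with the article's own description of the result as initial evidence.

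The cost is a few sentences and two further estimates, using measures already scheduled at the same time points. The downside is that the contrast has only modest power (about 0.57 for 0.8 SD against 0 under the assumptions above), so the specificity claim will probably be weaker.
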